### Population

#### Sample size

It is planned to include 237 cognitively healthy elderly subjects (aged 60 years and older) in total distributed over the three trial sites, satisfying the statistical power requirements for different research questions, as described below. Paticipants will be recruited by local newspaper announcements and flyers.

For the investigation of the primary objective, a sample size of 160 subjects has been determined based on a power calculation (see “Statistics”). Assuming a dropout rate of about 15%, the recruitment of subjects will be distributed as follows: Mainz: *N* = 60, Rostock: *N* = 60, German Sport University Cologne/University Hospital Cologne: *N* = 72.

For the investigation of the predictive value of a preceding ACT for the transfer of cognitive training gains in HOA (secondary objective), all 72 subjects recruited at the German Sport University Cologne/University Hospital Cologne (who are also part of the investigation of the primary outcome) will undergo an extended experimental protocol, including ACT followed by the cognitive training. The sample size of 72 subjects has been determined based on a power calculation (see “Statistics”). Since, so far, no evidence has been published showing that physical activity may have an impact on transfer via mechanisms other than brain structure and function, it is assumed that the preceding physical training in subjects recruited in Cologne will not confound the investigation of the primary objective.

To minimize/avoid bias, the following control subjects will be included: 15 HOA will be enrolled in Cologne undergoing the standard experimental protocol without ACT to assure that the net effect of the cognitive training does not differ from the effects at the other trial sites. To control performance alterations in the neuropsychological examinations for retest effects, an additional sample of 30 HOA, generated in Mainz (*N* = 10), Rostock (*N* = 10), and German Sport University Cologne/University Hospital Cologne (*N* = 10), will undergo the repeated neuropsychological examinations without cognitive training.

Within each trial site, participants will be distributed randomly to experimental or control groups, stratified centrally by the trial coordinator at the trial site University Medical Center Mainz. The study code is centrally managed by this trial site. Participants will be enrolled by their respective trial site.

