### Statistics

#### Sample size

Primary outcome: the analyses will focus on training gain transfer (defined as a binary criterion for each subject) and simultaneously incorporate measures of corpus callosum integrity and bihemispheric processing. The sample size calculation was performed based on main effects analyses where the effects of both measures will be considered as main effects. Assuming a transfer rate of cognitive training gains of about 15% for participants with low corpus callosum integrity, and a transfer odds ratio of 3 for participants with high corpus callosum integrity, a sample size of 160 provides a power of 0.8 at a significance level of 0.05 for a Wald Test in a logistic regression model. Assuming a dropout rate of about 15%, a total of 192 participants need to be included.

Secondary outcome: for evaluating physical training as a potential modulator of cognitive training gain transfer, ACT-induced fitness changes will be analyzed with respect to changes of corpus callosum integrity, as well as with respect to effects on transfer. The former analysis corresponds to considering the correlation between fitness changes and integrity changes. For the latter, an interaction between corpus callosum integrity and fitness changes with respect to transfer will be considered in a logistic regression model. Such an interaction can be expressed as a correlation between fitness changes and the degree of transfer in a group with low/high corpus callosum integrity. Based on the results by Voss et al. [14], we assume a correlation of about 0.43 between both measures. At a significance level of 0.05, 30 individuals per (equally sized) integrity group are needed to detect such a correlation with a power of 0.8. As a result, ACT needs to be performed for 60 individuals in total. Assuming a dropout rate of about 15%, 72 subjects at the German Sport University Cologne will undergo the extended experimental protocol.

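### The 30 per integrity group for the physical-training arm reaches power 0.8 only under an undeclared one-sided 0.05 test; at two-sided 0.05 the power is about 0.67 to 0.68

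*Protocol article*

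**What the plan says.** The secondary-outcome paragraph of the protocol article (Statistics, Sample size) relates ACT-induced fitness change to transfer through an interaction with corpus callosum integrity. It re-expresses that interaction as a correlation between fitness change and degree of transfer within a low- or high-integrity group. From a cited walking study it takes the effect size: "we assume a correlation of about 0.43 between both measures". It then states that "30 individuals per (equally sized) integrity group are needed to detect such a correlation with a power of 0.8", at a level of 0.05. Two groups of 30 give 60, and about 15% dropout gives 72 subjects at Cologne. The Population section repeats the basis for that number: "The sample size of 72 subjects has been determined based on a power calculation".

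The primary-outcome paragraph of the same section uses the same form of words for its level: "a sample size of 160 provides a power of 0.8 at a significance level of 0.05 for a Wald Test" in a logistic regression, with a transfer rate of about 15% at low integrity and an odds ratio of 3.

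Neither paragraph states sidedness, and neither does Analysis of secondary endpoints.

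**The concern.** A single correlation of 0.43 tested at the conventional two-sided 0.05 level needs clearly more than 30 observations for power 0.8. The stated figure therefore either uses a one-sided test without saying so, or overstates the power.

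This number is the only justification given for the size of the ACT arm. If the two-sided test is the one that will be run, the chance of missing the assumed correlation within an integrity group is about one in three, against the one in five that the text implies. Anyone who weighs a non-significant within-group result by the stated power would give it too much weight.

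**Working it through.** **Inputs** (all from Statistics, Sample size): r = 0.43, null value taken as 0; alpha = 0.05, sidedness not stated; power 0.8; n = 30 per group; dropout 15%; 72 recruited.

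**Method.** For a test of one correlation by Fisher's z, atanh(0.43) = 0.4599 and the standard error is 1/√(n − 3).

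**1. Power at n = 30.** 0.4599 × √27 = 2.390.
- Two-sided: Φ(2.390 − 1.960) = Φ(0.430) = 0.666.
- One-sided: Φ(2.390 − 1.645) = Φ(0.745) = 0.772.

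**2. Sample size for power 0.8.**
- Two-sided: ((1.960 + 0.8416)/0.4599)² + 3 = 40.1, so 41 per group.
- One-sided: ((1.645 + 0.8416)/0.4599)² + 3 = 32.2, so 33 per group.

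**3. Other methods,** to see whether the plan's figure depends on the approximation:

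| Method | Two-sided power, n = 30 | n for 0.8 | One-sided power, n = 30 | n for 0.8 |
|---|---|---|---|---|
| Fisher z | 0.666 | 41 | 0.772 | 33 |
| Fisher z, bias-corrected, t-based critical r | 0.679 | 40 | 0.784 | 32 |
| Exact bivariate normal | 0.681 | 40 | 0.786 | 32 |
| Noncentral t (two variants) | 0.682 to 0.712 | 39 to 37 | 0.792 to 0.816 | 31 to 29 |
| Simulated t-test, 400,000 runs | 0.681 | – | 0.786 | – |

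The plan's 30 is therefore reproduced, within rounding, only one-sided. To allow for an approximate 0.43, r was varied from 0.425 to 0.435. Two-sided power then runs from 0.65 to 0.72 and the required n from 36 to 42, so no two-sided variant gives 30.

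**4. Detectable correlation at n = 30, two-sided, power 0.8.** tanh(2.8016/√27) = 0.49 (0.47 to 0.49 across methods).

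**5. Does the dropout allowance cover the gap?** 60/0.85 = 70.6, so 72 is consistent with 60 completers. If all 72 completed (36 per group), Fisher z gives Φ(0.4599 × √33 − 1.960) = Φ(0.682) = 0.75; the other methods give up to 0.79. It does not.

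**6. Which sidedness does the primary calculation use?** An odds ratio of 3 on 15% gives odds of 3 × 0.15/0.85 = 0.529, a rate of 0.346. The plan gives no split of the 160, so assume 80 per integrity group. The standard error of the log odds ratio is √(1/(80 × 0.15 × 0.85) + 1/(80 × 0.346 × 0.654)) = 0.391, and ln 3/0.391 = 2.806.
- Two-sided: Φ(2.806 − 1.960) = 0.801.
- One-sided: Φ(2.806 − 1.645) = 0.877.

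Under the simplest reading, the primary figure of 0.8 is a two-sided one.

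**The case against.** **The power is not wrong without qualification.** A reader might infer that 30 per group simply cannot give 0.8. The document does not support that, because it leaves sidedness open. A one-sided test gives 0.786 by the exact distribution and 0.79 to 0.82 by noncentral t, which for a correlation of about 0.43 is 0.8 within rounding. The hypothesis is also directional: under Secondary objectives, the article expects coordination training to improve transfer. This stands, and it is why the defect is an undeclared one-sided level or, if two-sided was meant, an overstated power.

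**The two-sided reading of the primary calculation is an inference.** It assumes an equal split and ignores correlation between the two predictors. With 21% or 68% of subjects in the high-integrity group, one-sided power at N = 160 is also 0.80. With an equal split and an assumed predictor correlation of 0.45, one-sided power is 0.805 and two-sided 0.707. This stands too. The equal split remains the simplest reading, and the ACT calculation itself assumes equally sized groups, but the primary calculation does not prove the convention.

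**A pooled test looks like a way out, and is not one.** Over 60 completers, r = 0.43 has two-sided power Φ(0.4599 × √57 − 1.960) = 0.93 to 0.94. That holds only if the correlation is 0.43 in both groups, which means no interaction. If it were 0.43 in one group and 0 in the other, the pooled correlation would be roughly 0.215 and the power about 0.38. A pooled test also answers a different question from the planned interaction.

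**It is a secondary objective.** The primary sample size has its own calculation and is untouched. This limits the consequence but leaves the stated figure unsupported as written.

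**Conclusion.** The point holds in a conditional form. For r = 0.43, 30 per integrity group reaches roughly 0.8 only under a one-sided 0.05 test that the protocol article does not declare. At two-sided 0.05, power is about 0.67 to 0.68 (at most 0.71 by any method tried at r = 0.43). About 40 per group would then be needed, that is 80 to 82 completers and about 95 to 97 recruits at 15% dropout, against the stated 60 and 72.

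The arithmetic assumes a single-correlation test against zero and takes 0.43 at face value. That two-sided 0.05 is the document's convention rests on the primary calculation under an equal split, which is likely but not stated. Under either reading the sentence needs correction: it omits the sidedness it depends on, or it overstates power by about 12 to 13 percentage points.

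**What to change.** Keep the 72 subjects. State the sidedness of the 0.05 level for the ACT calculation, in line with the test that will be run, and restate the figure to match. For a two-sided test the sentence could read:

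> With 30 per integrity group, power is about 0.67 to 0.68 for r = 0.43 at two-sided 0.05; the correlation detectable with power 0.8 is about 0.49.

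If a one-sided test is intended, say so, give the reason, and quote its power (about 0.77 to 0.79). In both cases report the integrity-group correlations with confidence intervals, so that a non-significant result is read by its precision. Leave the planned integrity-by-fitness interaction in place and do not substitute a pooled correlation as the main test.

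The cost is one corrected sentence and a less favourable stated power. No subjects are added.

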#### Definition and analysis of primary endpoint

The primary endpoint is defined as the dichotomous outcome training gain transfer (Yes/No). Successful transfer will be defined as: (1) Performance improvement in a logical reasoning training task from the second to the last training session, (2) performance improvement in an untrained fluid intelligence transfer task (Leistungsprüfsystem, subtest 4) from the pre-cognitive-training phase to the post-cognitive-training phase, and (3) maintenance of the performance in the transfer task from post-cognitive-training phase to follow-up. Transfer task performance alterations have to be numerically greater than the mere retest effect of an untrained control group.

The primary endpoint will be analyzed using a logistic regression with measures of corpus callosum integrity and bihemispheric processing as independent variables. As a primary analysis, the effects of both measures will be considered as main effects. In subsequent analyses, we will take into account that bihemispheric processing may not be necessary for all participants, whereby strong training performance might specifically indicate such participants. This will be incorporated into the analyses by interaction terms and by allowing for non-linear effects. The models will be adjusted for age. In the primary analysis subjects with missing values will be excluded. Sensitivity analysis will be performed to evaluate the impact of the missing values.

The primary population is the intention-to-treat population. As a sensitivity analysis, an as-treated analysis will be performed. To investigate the center effects, center number will be additionally incorporated into the models.

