## Background

### Scientific background

Cognitive health has been consistently quoted as significant for life quality by older people and is regarded as an important contributor to late-life functioning [1, 2]. Patterns of cognitive change show great variation in healthy aging [3]. Cognitive training might contribute to enhance or preserve cognitive skills in cognitively healthy older adults (HOA). While improvements in cognition through training have been reported frequently in HOA, the capability to transfer cognitive training gains decreases with age [4–8]. Ideally, cognitive training would not only improve the function of trained cognitive tasks but also of untrained tasks of the same or a different cognitive domain (i.e., transfer of training gains). There is little evidence for successful transfer of cognitive training effects in HOA [6, 9]. Moreover, although transfer has been the subject of research for many years [10] the neurobiological mechanisms underlying the complex capability of transfer are still unknown. We recently demonstrated successful transfer of logical reasoning training gains to fluid intelligence immediately after a 4-week training in 71% of the HOA (*N* = 29 out of 41), but this effect persisted only in a subgroup of 22% over a 3-month follow-up period (*N* = 9 out of 41) [11].

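### The bar for successful transfer has no margin for individual measurement error, so chance alone could score about 12–33% of subjects as successes, a range that contains the planned low-integrity rate of 15% and the implied average of 24.8%

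*Protocol article*

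**What the plan says.** The Protocol article, Definition and analysis of primary endpoint, scores each subject Yes or No on three criteria:

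1. "Performance improvement in a logical reasoning training task from the second to the last training session".
2. Improvement on one untrained fluid-intelligence subtest (Leistungsprüfsystem, subtest 4) from before to after training.
3. Maintenance of that performance to the 3-month follow-up. No numerical rule is given for maintenance.

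The bar for the transfer task follows: "Transfer task performance alterations have to be numerically greater than the mere retest effect of an untrained control group". Population – Sample size supplies that group: "an additional sample of 30 HOA", ten per site, examined repeatedly without cognitive training.

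Statistics – Sample size first describes transfer as a binary criterion for each subject. Its starting point is: "Assuming a transfer rate of cognitive training gains of about 15% for participants with low corpus callosum integrity". For the high-integrity group it takes the odds of transfer to be three times as large. It concludes that "a sample size of 160 provides a power of 0.8 at a significance level of 0.05 for a Wald Test in a logistic regression model".

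Scientific background reports, for an earlier study of 41 people, immediate transfer in 71% (29 of 41), and that "this effect persisted only in a subgroup of 22% over a 3-month follow-up period" (9 of 41). The legend of Fig. 2 says that study also scored transfer as a gain beyond the retest effect in untrained elderly people.

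**The concern.** Subtracting the controls' retest effect removes the average practice gain. It does not remove the error in one person's score on one subtest taken once per visit. A trained subject who transferred nothing has a change centred on the controls' mean change, so a bar set at that mean, with any numerical excess counting, is close to a coin toss for that criterion. The other criteria, as worded, also ask for no minimum size.

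Two things are at stake. The first is the meaning of a Yes: an unknown share of scored successes are chance passes, and the secondary transfer models and the individual index of transfer likelihood use the same label. The second is the effect size: chance passes unrelated to corpus callosum integrity pull the odds ratio on the scored endpoint towards 1. The article describes no check of how often the rule would score an untrained person as a success.

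**Working it through.** **Reproducing the plan's figure.** Inputs from Statistics – Sample size: p1 = 0.15, odds ratio 3, n = 160, alpha 0.05, Wald test. Two-sided testing and a 1:1 split are assumed.

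- High-integrity odds = 3 × 0.15/0.85 = 0.529, so p2 = 0.529/1.529 = 0.346. Average = (0.15 + 0.346)/2 = 0.248.
- Variance term: 1/(0.15 × 0.85) + 1/(0.346 × 0.654) = 12.26.
- n per group = (1.960 + 0.842)² × 12.26/(ln 3)² = 79.7, total 159.5. Power at 160 is 0.801. The stated sample size is correct.

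**Chance rate with no true transfer.** Assumptions: the retest effect means the controls' mean change; trained and control subjects share the same average practice gain; errors e1, e2, e3 at the three visits are independent, with equal variance. A subject's stable ability cancels in the change score, so the test's reliability does not matter.

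- Pre-post bar alone: P(e2 > e1) = 1/2.
- Criteria 2 and 3, follow-up at or above post-training: P(e1 < e2 < e3) = 1/6 = 16.7% (simulation 16.6%).
- Criteria 2 and 3, follow-up only still above the bar: P(e1 is the smallest) = 1/3 = 33.3% (simulation 33.3%).
- If there is no average retest gain, the change must also exceed zero, and the figures fall slightly: 47%, 15% and 32%.

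The pass rate on criterion 1 is not in the document, so a range is assumed:

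| Criterion 1 pass rate | Chance rate, full endpoint |
|---|---|
| 1.0 | 16.7–33.3% |
| 0.9 | 15.0–30.0% |
| 0.8 | 13.3–26.7% |
| 0.7 | 11.7–23.3% |
| 0.5 (extreme) | 8.3–16.7% |

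Over 0.7 to 1.0 this is about 12–33%. It contains 15%, 24.8% and 22%. The planned high-integrity rate of 34.6% lies just above it.

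**Precision of the bar.** With 30 controls the standard error of their mean is 1/√30 = 0.183 SD of change. Shifting the bar by 1.96 × 0.183 = 0.358 SD moves the null share clearing it from 50% to between 36% and 64%.

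**Effect on the primary test, if 15% and 34.6% were true transfer rates.** Suppose every true transferrer is scored Yes and a fraction f of the others pass by chance. The scored rate is then p + (1 − p)f.

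- f = 1/6: 29.2% v 45.5%, odds ratio 2.03, Wald power 0.565 at n = 160.
- f = 1/3: 43.3% v 56.4%, odds ratio 1.69, Wald power 0.378.

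**What a margin would do.** With the bar at control mean + 1 SD of the controls' change (30 controls, no true transfer), simulation gives 16.8% clearing the pre-post bar and 3.5–6.9% meeting criteria 2 and 3. With the control mean and SD known exactly, the last range is 3.1–6.2%.

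**The case against.** The strongest reply is that the planning figures already include chance passes. Statistics – Sample size attaches the 15% and the odds ratio to a binary criterion for each subject, and the earlier study's 22% came from the same kind of rule. On that natural reading the power is 0.80, and adding false positives on top would count the dilution twice. This stands. The lower powers above hold only if the figures were meant as true transfer rates.

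It is also right that the primary question is whether brain measures predict the endpoint. Chance passes unrelated to those measures do not raise the type I error of that test.

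Three stronger conclusions that a reader might draw are not supported:

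- **That half of people without transfer are scored as successes.** The 50% applies to the pre-post bar alone. All three criteria must be met.
- **That a Yes cannot be read as transfer at all.** Overlap with a chance band that rests on assumptions does not show there is no signal. The earlier study's immediate rate, 29 of 41, tested against 50% gives an exact two-sided p of 0.012, which points the other way.
- **That power is far below 0.38.** This needs imperfect detection of true transferrers as well. For example, detection of 0.80 with a chance rate of 0.30 gives an odds ratio of 1.50 and power of 0.24. The document gives no gain size or measurement error from which to fix such inputs.

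One might also say the rule can be refined in an analysis plan. But the protocol text itself sets the bar as any numerical excess, so the weakness is in what is written.

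**Conclusion.** The point holds as a weakness in how the endpoint is defined. The bar carries no allowance for individual measurement error. With no true transfer, about 17–33% of subjects would meet criteria 2 and 3, and about 12–33% the full endpoint. The planned low-integrity rate and the implied average both fall inside that range, so the scored rate alone cannot show how much of it is transfer.

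The range rests on reading the retest effect as a group mean, on roughly symmetric and independent errors, on two readings of an undefined maintenance rule, and on an assumed 70–100% passing criterion 1. Ties on a coarse score would lower it slightly. A further average practice gain between post-training and follow-up (0.3 error SD in simulation) would raise the 17% to about 21%.

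The sample size is arithmetically correct, and the type I error of the primary test is not inflated. Power is 0.80 if the planning figures describe the scored endpoint, and about 0.38–0.57 (odds ratio about 1.7–2.0) if they describe true transfer, even with every true transferrer detected.

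**What to change.** 1. Apply criteria 2 and 3 unchanged to the randomised untrained controls, leaving each control out of the retest mean against which that control is judged. Report their pass rate, and the trained-minus-control difference on those same two criteria, with a confidence interval. Criterion 1 cannot be scored in people who did not train, so this is not the chance rate of the full endpoint. Keep it descriptive. Assuming 163 trained subjects (192 × 0.85), 26–30 controls and rates of 25% v 16.7%, the 95% half-width is about 15–16 percentage points. A rule that withheld the transfer label unless the difference was significant would have power of only about 18–19% in that case.
2. Pre-specify a sensitivity analysis of the primary logistic model with a reliable-change bar: control mean plus a multiple of the control SD of change, with the multiple fixed in advance. At + 1 SD, null passes on criteria 2 and 3 fall to about 3–7%. There will be fewer events, which is why it should not replace the primary analysis.
3. State in Statistics – Sample size that the 15% and the odds ratio of 3 refer to the scored endpoint, chance passes included, if that is what was meant.

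The cost is wording and a few added analyses. The controls are already planned for the repeated examinations, so no new data, visits or subjects are needed, and the primary analysis and sample size stay as they are.
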